### Child-Level positional interactions

CLPI will be used to assess children’s collective movement behaviour in the KG playground and to examine how spatial positioning relates to peer interactions and social engagement. Real-time spatial positioning will be continuously tracked during outdoor recess (~30 min) using high-resolution sensor technology, enabling the capture of detailed movement trajectories and interpersonal positioning within the playground environment.^49^ From these data, interpersonal movement-related variables will be derived to characterise patterns of proximity, coordination and interaction between children, providing insights into the relationship between movement dynamics and social behaviour. Outcomes will include mean inter-child distance and frequency of proximity interactions during recess.

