
### Outcomes and measures

Outcomes will be assessed using a multidimensional and multimethod approach, combining objective measures, standardised assessments and qualitative data, as summarised in table 1.

**Table 1 T1:** Overview of outcomes and measures used in the PLAY UP study, including primary, secondary and process outcomes, corresponding instruments, respondents and assessment time points (baseline and postintervention)

Outcome category	Outcome	Measure/instrument	Respondent/source	Time point
Primary outcome	Motor competence	Movement Assessment Battery for Children–Second Edition	Child	T0, T1
Secondary outcomes	Social, emotional and behavioural competences	Preschool and Kindergarten Behaviour Scales	Educator	T0, T1
	Behavioural difficulties	Strengths and Difficulties Questionnaire	Parent	T0, T1
	Executive functioning	Head-Toes-Knees-Shoulders Task	Child	T0, T1
	Spatial Activity Behaviour	Accelerometry+GPS	Child	T0, T1
	Child-Level Positional Interactions	Sensor-based positional tracking	Child/group level	T0, T1
	Kindergarten Affordances for Physical Literacy	Go-Exterior + Photo Elicitation Interviews	Research team/educators/children	T0, T1
Process outcomes (pilot phase)	Feasibility	Recruitment, retention, participation, attendance, adherence	Children, educators, research team	Pilot phase
	Acceptability	Observational records and interviews	Children, educators, research team	Pilot phase
	Implementation quality	Dose, intensity, duration, fidelity, resources, barriers/facilitators and safety	Educators, research team	Pilot phase

GPS, Global Positioning System; T0, baseline/initial assessment; T1, postintervention assessment.

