### Data analysis

Data analysis will be conducted using an integrative mixed-methods approach, combining quantitative and qualitative data, and will be performed separately for the pilot phase and the main study phase.

For the pilot phase, feasibility and acceptability indicators will be analysed descriptively, including recruitment, retention and attendance rates, as well as indicators related to implementation, resources and safety. Preliminary changes between baseline and postintervention will be explored using within-group comparisons, as appropriate.

For the main study phase, quantitative outcomes will be analysed by comparing the intervention and wait-list control groups at baseline and postintervention. The choice of statistical tests will be guided by the distribution and characteristics of the data. Where assumptions for parametric analyses are not met, non-parametric tests will be used to compare baseline differences between groups and changes from baseline to postintervention between groups.

Effect sizes will be calculated and reported to support interpretation of findings. The specific metric used will depend on the statistical tests applied, and effect sizes will be interpreted according to established guidelines. Results will be presented as means and SDs or means and 95% CIs, as appropriate.

All statistical analyses will be conducted using a significance level of p<0.05.

Qualitative data, including interviews and observational data, will be analysed using thematic analysis, and findings will be integrated with quantitative results to support interpretation of feasibility, acceptability and intervention effects.

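### CLPI outcomes are built from pairs of children, but their unit of analysis is left open: ordinary two-group tests on child scores would have a type I error of about 16–33%

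*Protocol article*

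**What the plan says.** - **Child-Level positional interactions:** the measure concerns the group ("CLPI will be used to assess children’s collective movement behaviour in the KG playground"), and its two quantities are named: "Outcomes will include mean inter-child distance and frequency of proximity interactions during recess". Tracking takes place during a recess of about 30 minutes. The section does not say whether one class or the whole kindergarten is tracked at a time.
- **Table 1 (Outcomes and measures):** the measure and source entries for CLPI read "Sensor-based positional tracking Child/group level".
- **Data analysis:** for the main phase, "quantitative outcomes will be analysed by comparing the intervention and wait-list control groups at baseline and postintervention". Then "The choice of statistical tests will be guided by the distribution and characteristics of the data", and where parametric assumptions fail, "non-parametric tests will be used to compare baseline differences between groups and changes from baseline to postintervention between groups". Finally, "All statistical analyses will be conducted using a significance level of p<0.05". CLPI is not exempted, and no class, kindergarten or pair term is named.
- **Abstract:** promises cluster-aware models. Data analysis does not take this up.
- **Study design and Sample size:** the comparison has one kindergarten of three classrooms per arm. The sample size is worked out for individual children.

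**The concern.** A distance or a contact between child A and child B counts in A's score and again in B's. Child scores built this way are correlated by construction, even when every child moves independently and no class or kindergarten effect exists. An ordinary two-sample test takes its standard error from the spread of child scores. That spread does not show the shared part, so the standard error is too small. A rank test has the same fault.

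With one kindergarten per arm, a p-value for CLPI can realistically come only from child or class scores. CLPI is the trial's only sensor-based measure of peer interaction outdoors, which the second aim sets out to explore. A nominally significant change in it could reflect the way the scores are constructed and not a change in behaviour, and a child-level confidence interval would be too narrow.

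**Working it through.** **The plan's own figure.** No error rate is given for CLPI beyond the nominal 0.05. The one computed figure is the sample size of 34. With f=0.25, two occasions and correlation 0.50, λ = f²·N·m/(1−ρ) = 0.0625·N·2/0.5 = 0.25N, on 1 and N−2 degrees of freedom. Power is 0.781 at N=32 and 0.807 at N=34, so 34 is reproduced. It is an individual-level calculation with no allowance for clusters or pairs.

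**Inputs.**
- From the documents: 215 children, about 75 of them in the pilot, two kindergartens left, three classes each. 215 − 75 = 140; 140/2 = 70 per arm; 70/3 ≈ 23 per class.
- Assumed: equal split, two-sided test, no intervention effect and, at first, no kindergarten, class or session effect.

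**Pair model.** Let d_ij = a_i + a_j + e_ij, with child effects a (variance σa²) and pair noise e (variance σe²). Each child's score is the mean of d_ij over the n−1 peers.
- True variance of the group mean: 4σa²/n + 2σe²/[n(n−1)].
- Variance implied by the spread of child scores: σa²·[(n−2)/(n−1)]²/n + σe²·(n−2)/[n(n−1)²].
- Ratio of true to implied: 2(n−1)/(n−2) ≈ 2 with pair noise only; 4[(n−1)/(n−2)]² ≈ 4 with child effects only.

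Neither limit depends on playground size, and both hardly depend on n.

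**Type I error** = 2·[1 − Φ(1.96/√ratio)].
- Ratio 2: 2·[1 − Φ(1.386)] = 16.6%.
- Ratio 4: 2·[1 − Φ(0.98)] = 32.7%.

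The child-level interval has 1/√2 ≈ 0.71 to 1/2 of its proper width.

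**Simulation on change scores (1,500 null trials per setting).**

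| Tracking | t-test | Mann-Whitney |
|---|---|---|
| 70 together | 16.5–35.7% | 16.5–33.7% |
| 3 classes of 23 | 17.1–32.4% | 16.5–31.7% |

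A separate simulation placed children on an assumed 30 × 20 m playground (800 trials, contact radius 3 m). It gave about 27–32% for distance and 18–27% for proximity counts. With an assumed 2 m radius, the t-test on proximity gave 14–19%.

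**Class means, 3 against 3 (4 df, 4,000 trials).** Tracked by class: 4.2–5.6%. Tracked together: 12.6–24.7%, because children in different classes still share pairs.

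**What adds to it.** An assumed kindergarten ICC on top of ratio 4 gives 2·[1 − Φ(1.96/√(4+69·ICC))]: 36.5% at ICC 0.01 and 47.3% at 0.05.

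**Does a pair-aware interval repair it?** A delete-one-child jackknife, with all children tracked together, rejected 4.9% when children moved independently. It rejected 31% when play groups of four shared a spot. With 3–5% variation between sessions it rejected 11–20% under one set of assumed settings and 19–32% under another. It corrects pair sharing and nothing else.

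**The case against.** The strongest reply is that no sentence in the article prescribes a test on child scores as independent units. Table 1 leaves child or group open, the abstract promises cluster-aware models, and test choice is to follow the characteristics of the data. The general sentence in Data analysis also covers GO-Exterior, which scores an environment, so it cannot mean a child-level test for every outcome. Scoring detail often sits in a separate analysis plan. With one group value per session the problem could not arise, and with classes tracked separately a class-level analysis would deal with it. The limitations and Sample size sections already advise caution about few clusters.

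Most of this stands as a limit on the claim. A reader might infer that the plan fixes a child-level test, and hence that it carries a false-positive rate of one in three. The documents do not support that: child-level testing is an inference, and the rate depends on an assumed pair model. The point is still not a mere omission. The article does state an approach for all quantitative outcomes, that approach does not suit outcomes it defines between children, and the abstract, Table 1 and Data analysis do not agree on the unit. The caution about few clusters does not address shared pairs.

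A reader might also infer that a jackknife or dyadic model would make the comparison valid. It would not: the article describes collective movement and warns of weather effects, and with one kindergarten per arm the between-kindergarten variance cannot be estimated.

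**Conclusion.** The concern holds in conditional form. Both CLPI outcomes are pair measures, and their unit of analysis is unresolved. If child scores go into ordinary parametric or rank tests, the type I error is about 16–33% under an additive pair model with about 70 children per arm and no kindergarten, class or session effect. This range is not an upper bound, since grouped movement, session differences or any kindergarten difference push it higher. The upper end applies when child effects dominate; in the playground simulations inter-child distance lay near it, and proximity counts were mostly lower.

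Class means hold the 5% level only if classes are tracked separately and the two kindergartens do not otherwise differ. CLPI is secondary and its aim is exploratory, so the MABC-2 result is untouched. The correction should be made before the data are analysed because it decides whether a CLPI p-value can be reported at all.

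**What to change.** In Data analysis:

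1. Exempt the two CLPI outcomes from child-level two-group tests, and quote no p-value computed from child scores.
2. Compute one pair-based mean distance and one pair-based contact frequency per separately tracked group and session.
3. State whether recess tracking is by class or by whole kindergarten, and change the Table 1 entry to match.
4. If classes are tracked separately, compare class-level changes between arms, with the existing caution about one kindergarten per arm. If they are tracked together, report the between-kindergarten difference in change descriptively.
5. Label any jackknife or dyadic interval as covering pair sharing only, not grouped movement, session variation or the confounding of arm with kindergarten.
6. Bring the abstract's promise of cluster-aware models into line with what Data analysis will do for CLPI.

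The cost is wording and a little code; no new data are needed. The downside is a wider interval, or a descriptive result, for this secondary outcome. Correcting for pair sharing alone widens the child-level interval by a factor of √2 ≈ 1.4 to √4 = 2.

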### KG affordances for physical literacy

The quality of the outdoor environment is assessed using the GO-Exterior instrument (original Portuguese version^50^), which is designed for application in early childhood education settings. The instrument involves direct observation of a group of children and the responsible educator in the outdoor space, typically over a period of approximately 60 min. GO-Exterior comprises two main components: (1) a structured observation grid and (2) a semistructured interview with the educator. The observation grid consists of 36 items organised into six analytical categories: (1) overall appearance and identity, (2) spatial dimension, (3) accessibility, (4) maintenance and safety, (5) action opportunities and (6) adult role and routines. Items are rated on a 3-point scale: 0 (‘not observed’), 1 (‘partially observed’) and 2 (‘observed’). In addition to quantitative scoring, each item includes a field for qualitative notes, allowing the observer to record contextual information that supports the assigned rating. The scoring system allows for the calculation of category-specific and overall scores, supporting the characterisation of the outdoor environment in terms of its quality, strengths and limitations. These data enable the identification of key areas for improvement and provide a structured basis for intervention planning.

To complement the observational data, a semistructured interview is conducted with the educator responsible for the observed group. This interview is carried out by the PI and aims to clarify and validate the observations, as well as to gather additional information regarding children’s use of the outdoor space, the role of adults in supporting outdoor play, family involvement and educators’ perspectives on outdoor learning. The information obtained through both components is integrated to develop a comprehensive profile of the outdoor environment. These data contribute to a more comprehensive understanding of how outdoor environments are used in practice and are used to support the interpretation of observational findings. In the context of the present study, the information gathered through the GO-Exterior instrument is also used to inform the design and refinement of the PLAY UP intervention.

PEI, following the approach proposed by Pyle,^51^ will be conducted to incorporate children’s perspectives into the research process and to support their active contribution to the intervention design. This method is particularly suitable for young children and is well established in early childhood research.

The interviews are conducted by the PI, a psychomotor therapist with extensive experience in child assessment. A photo elicitation technique will be used to explore children’s experiences in outdoor KG environments from their own perspectives. Prior to the interviews, children will take photographs in the outdoor space, capturing elements they perceive as meaningful for play and social interaction.

During the interviews, the child and the PI jointly examine and discuss these photographs, allowing the child to interpret and assign meaning to the images. This collaborative process facilitates child-centred data collection and enhances the depth of insights obtained.

The PI guides the conversation using open-ended questions focused on the child’s outdoor experiences, including where the child plays, the types of activities engaged in, interactions with peers and the environment, and perceptions of the outdoor space.

Particular attention will be given to: (1) preferences for physical environments that encourage or discourage engagement in both sedentary and physically active behaviours; (2) enjoyable experiences, sense of connection and appreciation of the environment in relation to movement and PA and (3) perceived physical and social affordances of the outdoor setting.

All interviews are audio-recorded and subsequently transcribed for analysis. Qualitative data will be analysed to generate insights that will inform the development and refinement of the PLAY UP intervention.

### Pilot phase: feasibility, acceptability and implementation quality

The study includes an initial pilot phase designed to assess the feasibility, acceptability and implementation quality of the PLAY UP intervention in outdoor KG settings.

This phase is being conducted in one KG (four classrooms), involving approximately 75 children, and will inform the refinement of the intervention prior to the main study phase.

Feasibility and acceptability will be assessed from multiple perspectives, including children, educators and the research team, using a combination of quantitative and qualitative methods.

Feasibility will be evaluated across several domains, including recruitment, retention and participation rates; access to participants and barriers to participation; attendance and adherence to intervention sessions; feasibility and suitability of assessment procedures and outcome measures; time and resources required to conduct assessments; adequacy of intervention dose, intensity and duration; and safety, including the monitoring and reporting of adverse events^52^. Acceptability will be assessed through indicators such as children’s engagement, participation and perceived enjoyment of the intervention, as well as educators’ and researchers’ perceptions of the intervention’s suitability and implementation. Additional qualitative data, including observational records and semistructured interviews with educators and children, will be collected to explore experiences, perceived benefits and potential areas for improvement.

Quantitative indicators (eg, recruitment, attendance and retention rates) will be analysed descriptively. Qualitative data will be analysed using thematic analysis, allowing the identification of key themes related to feasibility and acceptability.

This pilot phase corresponds to an exploratory, proof-of-concept stage, aimed at determining whether the intervention is feasible and acceptable. By addressing feasibility within a structured and evidence-based approach, this study will strengthen the intervention’s long-term impact, ensuring it remains accessible, adaptable and capable of promoting meaningful educational and developmental benefits.

### Sample size

The protocol includes an initial pilot phase involving approximately 75 children to assess feasibility, acceptability and implementation procedures.

For the main comparative phase, sample size was estimated using G*Power (F tests: analysis of variance repeated measures, within–between interaction). Assuming a moderate effect size (f=0.25), α=0.05, power=0.80, two groups, two measurement occasions (baseline and postintervention), a correlation among repeated measures of 0.50 and ε=1, the required total sample size was 34 children.

The overall recruited sample exceeds this individual-level requirement. Given the study design and the limited number of KG clusters in the comparative phase, findings related to intervention effects will be interpreted with caution, and effect estimates with CIs will be reported to support interpretation and inform future sample size assumptions.

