## Methods and analysis

### Study design

This study is a cluster-randomised trial, with randomisation at the kindergarten (KG) level, to be conducted in public preschools in Évora, Portugal. The trial includes three KG (clusters). One cluster (four classrooms) is being used in an initial pilot phase to assess feasibility, acceptability and implementation procedures. Following the pilot phase, the intervention will be implemented in the remaining two clusters (three classrooms each), with one assigned to the intervention condition and the other serving as a wait-list control group. The study follows a preintervention and postintervention assessment design. After the pilot phase, the two remaining KG will be randomised at the cluster level in a 1:1 ratio, with one allocated to the intervention group and the other to the wait-list control group. The random allocation sequence will be generated by an independent researcher not involved in recruitment, intervention delivery or outcome assessment, using a computer-generated randomisation procedure. Given the small number of clusters, simple randomisation will be used. The allocation will then be communicated to the research team responsible for implementing the intervention.

The initial pilot phase involves approximately 75 children from one KG, designed to assess the feasibility, acceptability and implementation procedures of the PLAY UP intervention.

The study commenced in January 2026 with recruitment and is currently ongoing, with completion scheduled for the end of June 2027. The intervention phase will consist of 15 sessions per classroom delivered over approximately 8–10 weeks, followed by postintervention assessments. The main comparative study phase will be implemented after completion of the pilot phase, following the same procedures.

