### Recruitment

Recruitment took place through informational sessions held during routine parent–educator meetings at the beginning of the second school term (January 2026). During these meetings, the research team presented the PLAY UP objectives, methodology and potential benefits. Parents received an information pack including the participant information sheet, informed consent form and the parent questionnaire to support informed participation.

Of the 218 potentially eligible children, two were excluded based on eligibility criteria and one declined participation, resulting in a final sample of 215 participants.

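### The 34-child requirement is correct for f=0.25, but in this interaction test f=0.25 is a 1.0 SD difference in change, which *moderate* does not convey; 0.5 SD needs 128

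*Protocol article*

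**What the plan says.** The Sample size section of the protocol article names the routine: "sample size was estimated using G*Power (F tests: analysis of variance repeated measures, within–between interaction". Its inputs are "α=0.05, power=0.80, two groups, two measurement occasions (baseline and postintervention", together with "a correlation among repeated measures of 0.50 and ε=1", and the effect is introduced with "Assuming a moderate effect size (f=0.25". The result is that "the required total sample size was 34 children". The section then says that the overall recruited sample is larger than this individual-level requirement. It asks for caution in reading intervention effects because there are few kindergartens.

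The sample is described elsewhere. Under Recruitment, two exclusions and one refusal are reported, "resulting in a final sample of 215 participants". Under Study design, "The initial pilot phase involves approximately 75 children from one KG", and for the main phase "the two remaining KG will be randomised at the cluster level in a 1:1 ratio". Data analysis treats the pilot and main phases separately. The strengths and limitations list calls the individual-level sample size adequate, while conceding that few clusters may limit power.

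The article does not translate f=0.25 into SD units or into points on the primary outcome, the MABC-2 total standardised score.

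**The concern.** Cohen's f is widely read through its labels. In a comparison of two group means, f=0.25 corresponds to a standardised difference of 0.5, which is where the label *moderate* comes from. The routine used here defines f for an interaction, and the same number then stands for a different difference between arms. A reader who sees f=0.25 called moderate will think that 34 children can detect a difference in change of about half an SD.

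What is at stake is how the sample size justification is read. Set against 34, the recruited sample looks several times larger than needed. If the effect of interest is nearer 0.5 SD, most of that surplus disappears. Anyone who reuses the paragraph to plan a similar trial would carry the misunderstanding forward.

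**Working it through.** **Inputs.** All are from the Sample size section unless noted:
- k = 2 groups, m = 2 occasions, correlation ρ = 0.50, ε = 1, α = 0.05, target power 0.80, f = 0.25
- equal arms (Study design gives 1:1 allocation of kindergartens; equal numbers of children per arm are assumed here)
- children in all phases: 215 (Recruitment)
- children in the pilot: about 75 (Study design)

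**Step 1: reproduce the plan's figure.** For the within-between interaction, λ = f²·N·m/(1−ρ), with (k−1)(m−1) = 1 and (N−k)(m−1) = N−2 degrees of freedom.
- N = 34: λ = 0.0625 × 34 × 2 / 0.5 = 8.5; power from F(1, 32) = 0.807
- N = 32: power = 0.781

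So 34 is the smallest even N that reaches 0.80. The stated figure is correct for the stated inputs.

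**Step 2: what f = 0.25 means here.** In this routine f is the root mean square of the interaction cell effects divided by the within-cell SD. If one arm changes by D more than the other, each of the four cells carries an interaction effect of ±D/4. Hence f = D/(4·SD):
- D = 1.0 SD gives f = 0.250
- D = 0.5 SD gives f = 0.125

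Cross-check with a two-sample t test on change scores. SD of change = SD × √(2(1−ρ)) = SD × √(2 × 0.5) = 1.0 SD. With 17 children per arm and D = 1.0 SD, power is 0.807, identical to step 1 (simulation: 0.80). Because ρ = 0.50 makes the two SDs equal, the 1.0 holds whether it is expressed in single-occasion SDs or in SDs of change.

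**Step 3: the requirement if the target is 0.5 SD.** Same inputs, f = 0.125:
- N = 126: λ = 0.015625 × 126 × 2 / 0.5 = 7.875; power = 0.795
- N = 128: λ = 0.015625 × 128 × 2 / 0.5 = 8.0; power = 0.801 (simulation: 0.80)

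The requirement is 128 independent children, 64 per arm.

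**Step 4: compare with the children available.** Comparative phase: 215 − 75 = about 140.
- Against 34: 140/34 = 4.1, about fourfold
- Against 128: 140/128 = 1.09, a margin of 12 children or about 9%
- Power for 0.5 SD at N = 140: λ = 0.015625 × 140 × 2 / 0.5 = 8.75; power = 0.836

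**Step 5: sensitivity.** The article gives no dropout rate, so these rates are illustrative assumptions. With 10% dropout (126 children) power for 0.5 SD is 0.795; with 20% (112 children) it is 0.746. The figure of 128 also depends on the assumed correlation. For 0.5 SD the required N is 178 at ρ = 0.3, 104 at ρ = 0.6 and 78 at ρ = 0.7.

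**The case against.** The strongest reply is that nothing has been miscalculated. The section names the routine and every input, and 34 is what the routine returns. The article never mentions 0.5 SD, and f=0.25 does carry the conventional label *moderate*. This stands. A reader might infer that 34 is only about a quarter of what the stated effect requires, but the stated effect is f=0.25, and 34 is exactly right for it. The figure of 128 applies only if *moderate* is taken to mean 0.5 SD, which is a reading of the word and not something the article states.

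A reader might also infer that the trial has low power for 0.5 SD, since 34 children would give only 0.293. No one plans a 34-child trial. With about 140 children the figure is 0.84 under independence.

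Nor does this point overturn the claims built on 34. About 140 exceeds 128, so the statement that the sample is larger than required survives, and this point alone does not require removing *adequate* from the strengths and limitations list.

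Finally, with one kindergarten per arm, no figure based on independent children gives the power of the actual comparison, and the article already urges caution about the number of clusters. That is true, but it is a separate matter, and the caution does not tell the reader what f=0.25 represents.

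What remains is that the label carries a meaning from a simple two-group comparison into an interaction, where the same f is twice as large a difference. Nothing in the article lets the reader see this.

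**Conclusion.** The point holds as a matter of labelling and interpretation, not of arithmetic. In the routine used, f=0.25 is a 1.0 SD difference in change between arms, and 34 children suffice for that. If the intended effect is 0.5 SD, the same inputs need 128 independent children. The comparative phase then exceeds its individual-level requirement by about 9% and not about fourfold, with power of about 0.84.

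These figures assume ρ = 0.50, equal arms, an analysis of change or its equivalent interaction test, no dropout and independent children. A different correlation or adjustment for baseline would change the 128. The correction is worth making because this paragraph is the article's only quantitative basis for its sample size. It is not critical, because the qualitative conclusion survives at the individual level.

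**What to change.** In the Sample size section:
- Drop *moderate* as the description of f=0.25 and state that, for this interaction, it corresponds to a 1.0 SD difference in change between arms.
- Add that a 0.5 SD difference (f=0.125, correlation 0.50) needs 128 independent children for 80% power.
- Compare the requirement with the roughly 140 children of the comparative phase, not with the overall 215.
- Say that neither 34 nor 128 allows for clustering or dropout.

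Possible wording: *For the interaction tested, f=0.25 corresponds to a 1.0 SD difference in change, for which 34 independent children give 80% power. A 0.5 SD difference (f=0.125) would need 128; about 140 children enter the comparative phase. Neither figure allows for clustering or dropout.*

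In the strengths and limitations list, *adequate* can stay if it is qualified as holding only under independence and, for 0.5 SD, with a thin margin.

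The cost is one rewritten paragraph and one qualifying phrase. The justification will look less generous, but enrolment, design and analysis are unchanged.
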